### Phase 2: Pilot RCT

#### Overview

The overall aim of phase 2 is to assess the feasibility and acceptability of iMI4HIV and prepare the necessary research infrastructure and processes for a future fully powered RCT to test its efficacy in increasing MI skills among CSS in HIV-related interactions. Thus, we will recruit 30 CSS and randomize them using a 2:1 ratio (VMI workshop + iMI4HIV vs VMI workshop + waitlist control).

Figure 1 presents an overview of the phase 2 RCT procedures, detailing an RCT with a waitlist control arm which will gain access to iMI4HIV after completion of the Follow-Up 1 assessment. This design allows us to achieve the specific aims of the study as well as gain initial insights into the effects of iMI4HIV on MI skills and how these skills may be retained after 3 months. After all participants complete a baseline computer-assisted self-interview (CASI), they will complete SPI-1, then take part in the VMI workshop. After that, they complete SPI-2 and are then randomized into iMI4HIV versus a waitlist control. After 4 weeks, all participants complete Follow-Up 1, which consists of SPI-3, a follow-up CASI, and for only those in the iMI4HIV arm a qualitative interview. This will allow us to assess the feasibility and acceptability of iMI4HIV among those who were randomized into that arm (n=20). At this assessment point, we will also explore the effects of iMI4HIV on MI skills by comparing MI fidelity ratings of the SPI-3 between the intervention and control groups.

After Follow-Up 1, those in the control arm will be given access to iMI4HIV; after 4 weeks, only this group will complete Follow-Up 2, which will consist of SPI-4, a follow-up CASI, and an in-depth interview, which will provide additional acceptability data. Participants originally randomized into iMI4HIV will undergo their Follow-Up 2 after 12 weeks (SPI-4 and CASI, no QI). This will allow us to gain insights into retention of MI skills after 3 months, a key data point for a subsequent efficacy trial of iMI4HIV in which we would want to assess maintenance of MI skills. Community-based organizations rarely offer MI coaching to staff after a training workshop. Thus, we will not offer MI coaching in either study arm to focus on assessing the preliminary effects of iMI4HIV on participants’ MI skills.

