##### Power Considerations

There is some controversy regarding the use of pilot data to estimate an actual effect size [111]; clinically meaningful effect sizes should be decided based on extrinsic, clinical judgment grounds, and not based on pilot data which are too few, typically, to obtain reliable conclusions. We can use pilot data to rule out unusually large or small true effects through standard 95% CI procedures. We will confirm that extrinsic effect sizes are contained within our CIs from the pilot. We will examine the distribution of each variable and calculate summary statistics by intervention condition. We will estimate key intervention parameters with sample means and proportions together with 2-sided 95% CIs and test the primary null hypotheses at the traditional 2-sided level α=.05 (to simulate the subsequent RCT). For planning the RCT, we will also consider 1-sided 90% confidence limits for mission-critical design parameters such as SDs and reference group end point rates and proportions in the conservative direction. This is because we intend to plan the sample size for the RCT so that power will be “excellent” (at least 80% power) for the clinically relevant effect size to be specified if our estimate of SDs is at the 1-sided 90% confidence limit in the conservative direction. This strategy will make proper allowance for the limited sample size of the pilot study with its consequent uncertainties, and still yield appropriate sample sizes for the future RCT. We will examine the strength of association between our primary outcome and key variables, with the view toward seeing if stratifying on such factors (eg, age and gender) would substantially reduce variability and increase the power of a future RCT. “Mission-critical” parameters include proportions for dichotomous end points; means and SDs for continuous end points; and response profiles for longitudinal studies. Large sample sizes are not required to locate these parameters approximately, but adequately, for planning the subsequent trial, whereas testing the study hypothesis in the pilot will generally not have sufficient statistical power. Estimation of mission-critical design parameters with point and CI estimates will be very important; continuous outcome measures make it feasible to detect promising effects even in small samples. For the continuous measures, means and SDs will be estimated. For approximately normally distributed variables, an upper 1-sided 90% confidence limit for the population SD, *s_U_*, will be constructed from *s_U_* = *s* × [(n – 1)/*x*^2^_0.10,_*_n_*_–1_]^1/2^, where *s* is the sample SD and *x*^2^_0.10,_*_n_*_–1_ is the upper 10th percentile of the chi-square distribution with *n* – 1 degrees of freedom. For approximately log-normally distributed variables, a logarithmic transformation will be applied to achieve approximate symmetry and normality. For the dichotomous variable, exact binomial methods will be used.

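### The upper 90% confidence limit for the SD is defined with the wrong chi-square tail, so it falls below the sample SD and would undersize the future RCT

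*Protocol article*

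**What the plan says.** The section Power Considerations (Methods, Quantitative Data Analysis) sets out how pilot estimates will feed the later trial. The RCT is to have high power, "if our estimate of SDs is at the 1-sided 90% confidence limit in the conservative direction". For approximately normal continuous measures the protocol promises "an upper 1-sided 90% confidence limit for the population SD". The formula is s_U = s × [(n − 1)/χ²_{0.10, n−1}]^½, where s is the sample SD. The text then explains the symbol in words: the χ² value "is the upper 10th percentile of the chi-square distribution with" n − 1 degrees of freedom. The article gives no numerical SD, effect size or RCT sample size.

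**The concern.** An upper confidence limit for a standard deviation must lie above the sample SD. Dividing by a chi-square value from the upper tail does the opposite, because that value is larger than its degrees of freedom and the square-root factor is below 1. The sentence therefore promises an upper limit and defines a lower one.

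This matters because the study is funded as a clinical trial planning grant, and SDs are among the parameters the section treats as critical to designing the next trial. The limit is meant to allow for the uncertainty of an SD estimated from a small pilot. Followed literally, the rule shrinks the SD, and it shrinks it most where the pilot gives the least information. That is worse than making no allowance at all.

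**Working it through.** **Inputs from the protocol article**

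- Limit wanted: 1-sided 90%, upper (Power Considerations).
- Chi-square value as worded: upper 10th percentile, that is the 0.90 quantile, on n − 1 df (same section).
- Future RCT: power of at least 80%, 2-sided α = 0.05 (same section).
- Pilot size: "we will recruit 30 CSS and randomize them using a 2:1 ratio", so 20 and 10 per arm (Phase 2, Overview). The article does not say which n enters the formula, so n = 30, 20 and 10 are all shown.

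**Step 1. The correct form.** Under normality (n − 1)s²/σ² follows χ² with n − 1 df. Let q be the value with P(χ² ≤ q) = 0.10. Then P[(n − 1)s²/σ² ≥ q] = 0.90. Rearranged, P[σ ≤ s × √((n − 1)/q)] = 0.90. The upper limit therefore needs the lower 10th percentile.

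**Step 2. The factor s_U/s under each definition.**

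| n (df) | χ² as worded (0.90 quantile) | Factor as worded | χ² correct (0.10 quantile) | Factor, correct |
|---|---|---|---|---|
| 30 (29) | 39.087 | √(29/39.087) = 0.861 | 19.768 | √(29/19.768) = 1.211 |
| 20 (19) | 27.204 | √(19/27.204) = 0.836 | 11.651 | √(19/11.651) = 1.277 |
| 10 (9) | 14.684 | √(9/14.684) = 0.783 | 4.168 | √(9/4.168) = 1.469 |

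For an SD pooled over both arms (28 df) the factors are 0.859 and 1.216.

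**Step 3. Coverage.** P(σ ≤ s_U) = P(χ² ≥ the value used). This is 0.10 as worded and 0.90 with the correct tail, at every n. The stated 90% level is not reproduced.

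**Step 4. Effect on RCT size.** For a fixed effect, the sample size for comparing two means is proportional to SD². No effect size is needed for these ratios.

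| n | Size as worded ÷ size using s | Size with correct limit ÷ size using s | Understatement |
|---|---|---|---|
| 30 | 0.861² = 0.74 | 1.211² = 1.47 | 39.087/19.768 = 1.98 |
| 20 | 0.836² = 0.70 | 1.277² = 1.63 | 27.204/11.651 = 2.33 |
| 10 | 0.783² = 0.61 | 1.469² = 2.16 | 14.684/4.168 = 3.52 |

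**Step 5. Effect on power.** The RCT truly has at least 80% power when the SD used for planning is at least σ. By Step 3 that happens with probability 10% as worded and 90% as intended.

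The median power follows from the median of χ². The planned size, divided by the size truly needed, has median χ²_0.50/χ²_0.90. In the normal approximation, power = Φ[(1.960 + 0.842) × √ratio − 1.960].

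- n = 30: ratio 28.336/39.087 = 0.725, power about 66%.
- n = 10: ratio 8.343/14.684 = 0.568, power about 56%.

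**Step 6. Illustration.** Assume an effect of 0.5 sample SDs and 1:1 allocation; both are assumptions, since the protocol leaves the effect size open. Sizes are for 80% power at 2-sided α = 0.05. Using s itself gives 63 per arm.

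| n | Per arm, as worded | Per arm, correct limit | Power of the as-worded size if σ is at the correct limit | Power of the as-worded size if σ = s |
|---|---|---|---|---|
| 30 | 47 | 93 | 52% | 68% |
| 20 | 44 | 103 | 45% | 65% |
| 10 | 39 | 136 | 32% | 60% |

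**The case against.** The best defence is that one word is wrong and the procedure is otherwise sound. The subscript 0.10 can be read as a cumulative probability, and the symbolic formula is then a correct upper limit. The surrounding text makes the conservative intent plain. An analyst who applied the definition literally would get an upper limit below the estimate and should notice. Nothing in the pilot depends on s_U: the primary outcomes are two proportions with their own progression thresholds, and dichotomous variables are handled by exact binomial methods. The RCT also needs a separate proposal, so no published number is wrong.

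Much of this stands, and it limits the consequence. The error lies in the verbal definition, the harm arises only if that definition is followed, and the pilot's conduct and results are untouched. It does not rescue the text. The subscript alone is ambiguous, but the sentence resolves the ambiguity in words, toward the wrong tail, and nothing elsewhere in the article corrects it. That the intent is clear is the reason to correct the definition that defeats it.

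**Conclusion.** The rule is wrong as written. The expression is a lower 1-sided 90% limit for the SD, with 10% coverage as an upper limit. If it is applied as worded, the future RCT is about 2 to 3.5 times too small relative to the intended limit (1.98 at n = 30, 2.33 at n = 20, 3.52 at n = 10). It is also smaller than if the sample SD had been used unadjusted.

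The size ratios follow from the formula, with no assumed SD or effect size. The coverage and median-power figures assume approximate normality, which the protocol itself requires for this formula. The power figures also take the effect size as correctly specified. The per-arm numbers are illustrations at an assumed effect. This should be corrected before any pilot SD is used for planning.

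**What to change.** Replace the definition of the quantile with the lower 10th percentile of the chi-square distribution on n − 1 df, written explicitly as the q with P(χ² ≤ q) = 0.10 (for example 19.77 for 29 df).

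Two additions are optional:

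- A check that s_U exceeds s, which catches a tail error at once.
- A statement of which SD and df are used. If the within-arm SD is pooled over the two arms, use n − 2 = 28 df (factor 1.216).

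The cost is one sentence in the protocol or SAP and no change to the pilot. The RCT sample size planned from s_U will be larger than under the present wording, as the section intends.

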
### Ethical Considerations

The study was reviewed and approved by the Florida State University (FSU) Institutional Review Board (ID: STUDY00004477). This study does not assess health-related biomedical or behavioral outcomes; thus, it does not meet NIH criteria for a clinical trial and will not be registered in ClinicalTrials.gov.

All participants are provided with a written informed consent form to read before participating in the study. The consent form includes an overview of the study, study procedures, risks of participation, procedures to minimize risks of participation, a statement of voluntary participation, and contact information for the principal investigators, along with contact information for the FSU Institutional Review Board.

The results of the study may be published or presented, but no information that can identify individual participants will ever be provided or released in publications or presentations. To protect the privacy and confidentiality of participants, the study staff will keep any records containing identifying information in a locked cabinet accessible only to the research staff. The computer programs used in tablet-based interventions are compliant with US regulations on personal health information, as are the servers on which the data are stored. All data captured on the tablet, although it do not include identifying information, are encrypted in transit to maintain confidentiality. Any other study data will be stored on a secure computer that is protected by passwords. All records will be kept confidential. This is consistent with the guidelines of the US NIH. After removing all identifying information, the remaining deidentified information collected during the study could be used for future research studies or distributed to another investigator for future research studies without additional consent.

All participant incentives will be paid via gift cards. In phase 1, FG participants received US $75; agency leaders received US $100 for the interview; and iMI4HIV pilot participants will receive US $50 plus the opportunity to win a US $250 prize for completing the intervention within the 4-week allotted period. This incentive is provided to motivate the timely completion of the online training program among these participants to inform any final revisions that are necessary before the phase 2 RCT; main study outcomes are based on the phase 2 RCT results, which do not include this raffle incentive. Phase 2 RCT participants will receive up to US $205 for completing questionnaires (3 timepoints), 4 standard patient interactions, and a qualitative interview.

## Results

The study launched in February 2024. During the summer of 2024, we conducted 2 FGs (n=11) and QIs (n=8) with HIV Care Agency Leadership to inform the content and interactive components of the iMI4HIV. Preliminary findings from the FGs and QIs were shared with the CAB and expert consultants. In the Fall of 2024, we recorded a series of training videos focused on using MI in key HIV care interactions. Since then, we have been developing the content and layout of the training program. We expect to conduct the phase 1 pilot study in the Fall of 2025 and the pilot RCT during 2026.

## Discussion

### Overview

To address the need for online MI training geared specifically for the HIV care setting, this mixed methods study seeks to develop iMI4HIV, an interactive, gamified, online MI training program specifically tailored for CSS to improve their MI skills in HIV care communications. The goal is to train CSS to deliver MI competently so they can integrate MI into their health care communications with individuals seeking or receiving HIV-related services (status-neutral). If successful in building MI skills among CSS, iMI4HIV has the potential to shift how MI training is provided to CSS who work in HIV care settings. Furthermore, the program can be housed at FSU for use by AETCs throughout the country to provide additional MI training to their client agencies, used to train HIV treatment counselors in research studies, and provide training opportunities for other community-based agencies working to end the HIV Epidemic.

### Strengths

This proposed study has numerous strengths. First, contrary to the currently available simulations for MI training, iMI4HIV will offer an innovative, sequenced approach to comprehensive online MI training with a range of interactive and gamification components used in novel ways to build key MI technical skills. As such, it will also be the first to assess user acceptability, feasibility, and engagement of this new approach to online MI training. Second, at an expected 8-10 hours, iMI4HIV will be the first and most comprehensive interactive online MI training that addresses the full status-neutral HIV care cascade. The only existing interactive HIV-focused MI training is approximately 1 hour in duration and only addresses treatment adherence counseling for nurses. Third, this is the first online MI training study to systematically engage targeted end users throughout the development and testing process to obtain their feedback for revisions. Fourth, based on current scientific literature, this study will be among the first to conduct a rigorous assessment of efficacy (even within an underpowered RCT).

### Limitations

Although we anticipate high interest in MI training and iMI4HIV, recruitment and retention challenges can always arise and we consider these the main potential challenges to this study. Additionally, acceptability data (both quantitative and qualitative) are subject to social desirability. To minimize this risk, we will highlight for participants the importance of openly sharing their experiences and opinions, whether positive or negative.

### Conclusions

As designed, this study specifically responds to the Notice of Special Interest: Advancing Health Communication Research on HIV Prevention, Treatment and Cure (NOT-MH-21-105) announced by NIH, which includes an interest in studies that seek to “optimize effective communication and engagement practices between PLHIV and healthcare providers.” This R34 begins to address a critical need for novel approaches to train CSS in MI, a counseling or communication approach with proven efficacy in improving health care outcomes across the HIV care cascade. With its focus specifically on MI in HIV care interactions, iMI4HIV gives CSS in HIV care settings an invaluable opportunity to solidify MI skills gained during MI training workshops. Furthermore, as an asynchronous training program, iMI4HIV provides significant flexibility in when it can be completed, increasing accessibility to potential users. If findings on feasibility (≥70% of participants complete the iMI4HIV modules within 4 weeks) and acceptability (≥80% of participants rate iMI4HIV a “4” or “5” on the TFA overall acceptability rating) are favorable, we will submit a proposal for a fully powered RCT to assess the efficacy of iMI4HIV to achieve MI competence. In that study, we may even consider a study arm using an expanded version of iMI4HIV to allow for fully asynchronous MI training, which was cost-prohibitive in this study.

## Appendix

Multimedia Appendix 1 Peer-review report from HIBI - HIV/AIDS Intra- and Inter-personal Determinants and Behavioral Interventions Study Section, Risk, Prevention and Health Behavior Integrated Review Group (National Institutes of Health, USA).

## Abbreviations

AETC: AIDS Education and Training Center
CAB: Community Advisory Board
CASI: computer-assisted self-interview
CHW: community health worker
CSS: counseling support staff
EBP: evidence-based practice
FG: focus group
FSU: Florida State University
HCC: HIV Care Continuum
HIPAA: Health Insurance Portability and Accountability Act
iMI4HIV: internet-based motivational interviewing training program for HIV counseling support staff
MI: motivational interviewing
MIKAT: Motivational Interviewing Knowledge and Attitudes Test
MITI: Motivational Interviewing Treatment Integrity
NECA AETC: Northeast and Caribbean AIDS Education and Training Center
NIH: National Institutes of Health
QI: qualitative interview
RAD: Rapid Application Development
RCT: randomized controlled trial
SPI: Standard Patient Interaction
TFA: Theoretical Framework of Acceptability
UCRAD: User Centered Rapid Application Development
VMI: virtual motivational interviewing
